#### Analysis of Video-Recorded Data

We will code video-recorded data using behavioral analysis software (Observer XT version 12.0; Noldus Information Technology) [51] to capture potential indicators of movement confidence (eg, hesitation) and how these change over time. Behavioral analysis of video-recorded data involves creating a coding scheme with operationalized definitions to objectively code the data. Coded data can capture the frequency and duration of events and behaviors, such as how often confident or nonconfident behaviors occur. This will allow for the extraction of count and percentage data related to movement confidence (eg, 20% of turns were completed confidently during week 1, which increased to 80% by week 10).

We will develop the movement confidence coding scheme using information from 2 distinct sources: (1) previous studies that examined movement confidence (eg, [13,14,16]), and (2) observations from previous work with motion-based technology and people with dementia or MCI (eg, [36,37]). For instance, Dove and Astell [36] noted that people with dementia or MCI from an adult day program appeared to move more confidently with repeated exposure to the movement situation (ie, playing Xbox 360 Kinect bowling). That is, participants gradually transitioned from hesitant, rigid movements to relaxed, flowing movements and relied less on the instructor to complete the movement task. Indeed, over time, participants required fewer prompts (eg, verbal, gesture) and less physical support from the instructor to complete the movement task [36]. Additionally, some participants became less reliant on their mobility devices and began to develop a professional-looking bowling stance.

Video recordings will be coded by 4 independent raters, 1 of whom is the first author (ED). Prior to formally coding the videos for analysis, each rater will undergo training using the Observer XT video analysis software [51] and the movement confidence coding scheme. This will involve completing an introductory coding exercise, reviewing the video-recorded data, familiarizing themselves with the coding scheme and its operational definitions, and practicing coding the videos. We will compare the practice work of each coder for consistency using interrater reliability analysis to determine whether the 4 raters are reliably evaluating the same material [52]. This will also reduce the likelihood of researcher bias, given that the work of the other 3 raters will be compared for consistency against that of the fourth rater (ED), who is also involved in facilitating the study intervention and conducting the pretest and posttest measures. Once interrater reliability between the 4 raters reaches at least 80% agreement, the 4 raters will formally code the video recordings for analysis. This involves dividing up the coding so that each rater will be responsible for coding 1 of the 4 study sites (ie, 6 sessions per rater).

We will analyze all 6 video recordings from each data collection site. These comprise recordings of the first 2 sessions (1 and 2), the middle 2 sessions (11 and 12), and the final 2 sessions (19 and 20). Each rater will code the entirety of each selected session (60 minutes), with each bowling turn of each participant analyzed. Then, we will combine coded data from the 6 sessions into 3 respective time points: start (T1) = the first 2 sessions, midpoint (T2) = the 2 middle sessions, and end (T3) = the last 2 sessions.

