**Methods:**

In this quasi-experimental pre- and posttest design, we will recruit 24 people with dementia or mild cognitive impairment from 4 adult day programs and invite them to play Xbox Kinect bowling in a group setting, twice weekly for 10 weeks. We will require participants to speak and understand English, be without visual impairment, and be able to stand and walk. At pretest, participants will complete the Mini-Balance Evaluation Systems Test (Mini-BESTest) and the Montreal Cognitive Assessment (MoCA). We will video record participants during weeks 1, 5, and 10 of the intervention to capture behavioral indicators of movement confidence (eg, fluency of motion) through coding. At posttest, the Mini-BESTest and MoCA will be repeated. We will analyze quantitative data collected through the Mini-BESTest and the MoCA using an intent-to-treat analysis, with study site and number of intervention sessions attended as covariates. To analyze the videos, we will extract count and percentage data from the coded recordings.

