### Objective

Despite these promising results, the impacts of interventions using motion-based technology are relatively unknown for this population. In their review of the efficacy of motion-based technology interventions for people with dementia with regard to cognition, physical function (eg, strength), emotional well-being, social health, and quality of life, van Santen and colleagues [38] identified only 3 randomized trials. We designed this study to extend knowledge of the potential of motion-based technology in rehabilitation for people with dementia or MCI. Specifically, we will examine the impacts of a group motion-based technology intervention on balance, movement confidence, and cognitive function among people with dementia or MCI. The specific hypotheses of the study reflect these aims. Hypothesis 1 states that balance will show statistically significant improvement after the motion-based technology intervention, as measured by the Mini-Balance Evaluation Systems Test (Mini-BESTest). Hypothesis 2 states that movement confidence will improve after the motion-based technology intervention, as measured by the analysis of coded video-recorded footage taken of participants during the intervention sessions (eg, number of turns completed confidently). Hypothesis 3 states that cognitive function will show statistically significant differences after the motion-based technology intervention, as measured by the Montreal Cognitive Assessment (MoCA).

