#### Analysis of Test and Questionnaire Data

All analyses will follow an intent-to-treat approach, whereby we will base the results of the experiment on all participants recruited to take part in the intervention, and not just those who complete the intervention [49]. This approach to analysis will provide a more reliable estimate of the true effectiveness of the motion-based technology intervention, by reproducing what occurs in real-world settings such as community-based adult day programs. We will handle missing data using multiple imputation, which is the recommended standard for accounting for missing research data when working with people who have dementia [50]. We will include study site and the number of intervention sessions attended by the participants in the statistical model as covariates. These analyses will be conducted using IBM SPSS version 26 (IBM Corporation), using a *P* value of <.05 and a confidence interval of 95%.

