Broadly, we expect that this research will be relevant to scientific, clinical, and professional audiences. For example, we expect that this research will be relevant to scholarly rehabilitation practice, advocacy, or advancing understanding of occupation (ie, meaningful activity) as a fundamental social determinant of health and well-being for people with dementia or MCI. Understanding the potential impacts of using motion-based technology with people with dementia or MCI can inform future evidence-based, community-based rehabilitation practice. That is, if participants show significant improvements in balance, movement confidence, and cognitive function as a result of partaking in the motion-based technology intervention, there is the potential of motion-based technology systems being incorporated into rehabilitation interventions targeting these outcomes. Additionally, we expect that this study will demonstrate the feasibility of using motion-based technology to deliver task-specific interventions to people with dementia or MCI. This is relevant given that tasks and goals of importance to clients are often used to inform rehabilitation interventions. Finally, this research aims to advocate the inclusion of people with dementia or MCI in rehabilitation science and interventions. We expect that this study will demonstrate the ability of people with dementia or MCI to engage in meaningful activity and emphasize the importance of meaningful activity to support health and well-being of people with dementia or MCI.

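### Hypothesis 2 predicts that movement confidence will improve, but its stated analysis is descriptive only, with no measure of uncertainty and no criterion, so it cannot support the significant improvement that the Discussion envisages

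*Protocol article*

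**What the plan says.** The protocol article words its three hypotheses differently (Introduction, Objective):

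- Hypothesis 1: "balance will show statistically significant improvement after the motion-based technology intervention".
- Hypothesis 2: "Hypothesis 2 states that movement confidence will improve after the motion-based technology intervention", to be measured from coded video.
- Hypothesis 3: "cognitive function will show statistically significant differences after the motion-based technology intervention".

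The analysis follows the same split. The Abstract (Methods) gives the Mini-BESTest and MoCA an intent-to-treat analysis with covariates, and says of the videos: "To analyze the videos, we will extract count and percentage data from the coded recordings". In the body, the inferential standard stands under Analysis of Test and Questionnaire Data: "These analyses will be conducted using IBM SPSS version 26 (IBM Corporation), using a *P* value of <.05 and a confidence interval of 95"%.

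The separate section Analysis of Video-Recorded Data describes a coding scheme and its output: "This will allow for the extraction of count and percentage data related to movement confidence". Its illustration is "20% of turns were completed confidently during week 1, which increased to 80% by week 10". It then combines the six recorded sessions per site into T1, T2 and T3. It names several possible indicators and singles out none as the main one.

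The Discussion (Comparison With Prior Work) foresees a role in rehabilitation "if participants show significant improvements in balance, movement confidence, and cognitive function as a result of partaking in the motion-based technology intervention".

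**The concern.** Hypothesis 2 is directional, so someone must eventually say whether the data support it. The analysis described yields percentages at three times with nothing to show how much they would vary if nothing had changed. A rise of a given size could be a real change or ordinary variation between sessions and between turns, and the stated output does not distinguish the two. This holds even with complete data and perfectly consistent raters, so it is separate from attrition, practice effects and coder bias.

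Two things are at stake. First, one of three hypotheses could be reported as confirmed on a lower standard of evidence than the other two, with the standard chosen after the results are seen. Second, the Discussion's wording about significant improvement in movement confidence would have no analysis behind it.

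**Working it through.** **1. The plan's own figure.** The only sample-size figure concerns the Mini-BESTest (Participants section): effect size 0.8, two-tailed alpha .05, power 80%, at least 15 participants, raised to 24 for 40% attrition. A paired t test with standardised change 0.8 gives power 0.790 at n = 14 and 0.821 at n = 15, so 15 is reproduced. With 40% loss, 24 × 0.6 = 14.4 remain. The calculation does not extend to movement confidence, and no error rate or sample size is given for Hypothesis 2. It does set the plausible range of n: 14 to 24.

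**2. Criterion and analysis side by side.**

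| | Required result | Stated analysis | Uncertainty stated |
|---|---|---|---|
| Hypothesis 1, balance | significant improvement | model with site and sessions attended | P<.05, 95% CI |
| Hypothesis 2, movement confidence | improvement | counts and percentages at T1–T3 | none |
| Hypothesis 3, cognition | significant difference | model with site and sessions attended | P<.05, 95% CI |

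The Discussion sentence treats all three outcomes as if they were in the first row.

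**3. What the error rate would be under different readings.** The protocol gives no rule, so each line assumes one. The video inputs are also assumptions: 10, 20 or 40 turns per person per time point; 20%, 50% or 80% of turns confident; logit-scale SDs of 1 between persons and 0.5 between occasions within a person; n = 15 or 24; no true change; 20,000 simulated trials per setting.

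- Any rise from T1 to T3 in one indicator: by symmetry 0.5 − (probability of a tie)/2. Ties occur in 0.01–0.05 of trials, giving about 0.475–0.495; simulated 0.47–0.50.
- Any one of k independent indicators rises: 1 − 0.5^k = 0.75 (k = 2), 0.875 (k = 3), 0.97 (k = 5). At correlation 0.5 the simulated values are 0.67, 0.74 and 0.83.
- All k independent indicators rise: 0.5^k = 0.25, 0.125, 0.03.
- Strictly ordered T1 < T2 < T3 in one indicator, if the three values are exchangeable: 1/3! = 1/6.
- A rise of at least 10 points in one indicator: 0.00–0.06. At n = 14 with an occasion SD of 1.0 it is a little above 0.1.
- A rise as large as the 20% to 80% illustration: practically never.

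**4. What a within-participant analysis would do.** A paired test of each participant's T3−T1 change at two-sided .05 declares improvement in 0.022–0.025 of the null trials in step 3, and a change in either direction in 0.046–0.051. Treating pooled turns as independent is not a substitute: for n = 14–24, 10 or 20 turns, a 50% baseline and an occasion SD of 0.5 or 1.0, a pooled two-proportion test rejects in about 8–30% of null trials.

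**5. Power of that analysis, n = 14, 10 turns.** For a shift as in the illustration (20% to 80% for a typical participant), power exceeds 0.99. For 50% to 70% it is about 0.65 with an occasion SD of 0.5 and 0.37 with 1.0.

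**The case against.** The strongest reply has three parts.

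**A condensed article may leave the test to a fuller document.** That would excuse silence. Here the article states the video analysis twice and, both times, sets it apart from the inferential analysis of the other outcomes. A fuller plan could supply a test, but the published hypothesis, analysis and Discussion would still not agree.

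**A descriptive plan may be deliberate.** The Mini-BESTest is the primary outcome, and the Limitations section calls the video evaluation pilot work that may miss aspects of movement confidence. Leaving out the word significant from Hypothesis 2 fits that. This part stands: descriptive reporting of a pilot measure is not an error. But the pilot remark concerns how well the method captures the construct. It neither makes Hypothesis 2 descriptive nor qualifies the Discussion. That sentence is conditional, and it is not an analysis criterion; even so, the stated analysis could never show its condition to be met for movement confidence.

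**No decision rule is written.** This part also stands. A reader might infer that Hypothesis 2 counts as supported whenever the T3 percentage exceeds the T1 percentage, and so that the plan declares improvement about half the time when nothing has changed. The documents do not say this. The 20% to 80% figure is introduced as an example, and the three time points come with no comparison rule.

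**Conclusion.** The point holds as a mismatch between hypothesis, analysis and envisaged conclusion. A directional hypothesis is given only a descriptive analysis, with no uncertainty and no criterion, beside two hypotheses held to P<.05 with a 95% interval. That analysis cannot separate change from chance and cannot yield a significant improvement in movement confidence.

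The 47–50% false-positive figure is conditional on an assumed rule (any rise in one indicator) and on assumed turn counts and SDs. It is not a property of the plan as written. Other readings run from about 0 to 0.97, and a change as large as the protocol's example would hardly be mistaken for chance under these assumptions. The spread is itself the reason to act: with no criterion fixed, the error rate depends on what is chosen later. The point concerns a non-primary outcome and leaves the Mini-BESTest analysis untouched.

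**What to change.** Choose one of two routes. The article says that data analysis is under way, so the choice should be made before the video results are interpreted.

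**Inferential route.** In Analysis of Video-Recorded Data, name one main indicator for Hypothesis 2, for example the percentage of turns completed confidently. Compute it for each participant at T1, T2 and T3. Report the mean within-participant T3−T1 change with a 95% confidence interval, from a paired analysis or a mixed model with a participant random effect, and not from pooled turns treated as independent. State that Hypothesis 2 is supported only if the interval lies wholly on the side of improvement. Label all other indicators descriptive.

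**Descriptive route.** Restate Hypothesis 2 as a descriptive aim and remove movement confidence from the Discussion sentence on significant improvements.

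Either route costs a few sentences; the first adds one analysis of data already being coded, with no new participants or recordings. Its small downside is that a modest rise may be reported as inconclusive at this sample size (the 0.37–0.65 power above). The interval deals with chance only; it does not answer questions about attrition, practice effects or the lack of a control group.

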### Intervention Description

We will invite participants to take part in a 10-week motion-based technology intervention (Xbox Kinect bowling), held in a group setting at 4 community-based adult day programs. The intervention sessions will take place twice per week for 10 weeks (20 sessions per site). Sessions will be facilitated by the first author (ED) using teaching techniques successfully employed in previous studies involving motion-based technology and people with dementia or MCI, such as verbal prompts, gesture demonstrations, and physical assistance [37]. During each session, approximately six participants will be seated together in a room and will each have a turn to engage with the technology and game. The facilitator will call upon each participant in the group 1 at a time to take their turn, which will continue for the duration of each session (approximately 60 minutes). While the active player is engaging with the technology, the rest of the group will sit and observe.

The motion-based technology system to be used in this study is the Xbox One Kinect (Microsoft Corporation). We chose the Xbox One Kinect over other commercially available motion-based technology systems (eg, Nintendo Wii) given that interaction with this system requires no handheld controller and relies purely on naturalistic movements (eg, waving an arm). We will used the commercially available bowling game offered through the Kinect Sports Rivals package in the study, alongside the Xbox One Kinect. We chose the Kinect Sports Rivals bowling game given that the game of bowling is generally familiar.

To partake in the intervention, participants are required to rise from their chair, walk to the line (ie, a piece of black electrical tape placed on the floor in front of the technology to cue participants regarding where to stand), play the bowling game, walk back to the chair, and sit down. We will break down the movements required to play the bowling game for participants in a stepwise manner: (1) raise an arm above the head to activate the Kinect sensor; (2) reach the same arm out to the side; (3) close the hand of the extended arm to pick up a bowling ball; (4) extend the same arm back behind to wind up; (5) open the hand of the same arm to release the ball; and (6) swing the same arm forward to throw the ball.

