### Data Analysis

#### Inclusion in Data Analysis

We will amalgamate data collected from all 4 adult day programs for analysis and reporting purposes. We will encourage participants to attend as many of the intervention sessions as possible; using an intent-to-treat approach, we will include all participants in the final analysis (with number of sessions as a covariate), regardless of the number of intervention sessions they attended. Participants who miss sessions will still be permitted to participate in the motion-based technology intervention. Makeup sessions for participants who are not able to attend all sessions will not be offered. Participants who miss sessions will be accounted for during the analysis.

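### Turn counts, and a percentage taken over all turns, can shift with who attends, so they are unsafe evidence for Hypothesis 2 on movement confidence

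*Protocol article*

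**What the plan says.** Under Objective, Hypothesis 2 says that movement confidence will improve, judged from coded video, with "number of turns completed confidently" as the example measure. The abstract's Methods paragraph gives the whole video analysis in one sentence: "To analyze the videos, we will extract count and percentage data from the coded recordings". Analysis of Video-Recorded Data illustrates the result as "20% of turns were completed confidently during week 1, which increased to 80% by week 10". It then says "we will combine coded data from the 6 sessions into 3 respective time points": T1 (sessions 1 and 2), T2 (11 and 12) and T3 (19 and 20). Coding is done "with each bowling turn of each participant analyzed". Inclusion in Data Analysis adds: "We will amalgamate data collected from all 4 adult day programs for analysis and reporting purposes".

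Three other statements bear on this:

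- Intervention Description seats about six people per session and calls them up one at a time, a rota "which will continue for the duration of each session (approximately 60 minutes".
- Participants and Limitations expect 40% attrition, with prolonged illness and moves to long-term care as examples. Participants also names absenteeism. Makeup sessions are not offered.
- Study Design describes a within-participants study.

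**The concern.** The number of turns a person takes depends on how many others are in the room. If the group shrinks while the session stays at about an hour, each remaining player comes up more often. A count of confident turns per player then measures attendance as well as confidence.

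A percentage does not have that defect, but its meaning depends on the denominator. If it is taken over all turns at a time point, T1 includes people who have left by T3. Should they differ in confidence from those who stay, the figure moves although no individual has changed.

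In either case a change in who was filmed could be reported as a change in movement confidence, in a study designed to compare people with themselves.

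**Working it through.** **Plan's own figure.** The article gives no numerical target for movement confidence. The 20% to 80% in the video section is only an example, so there is no calculation to reproduce. The sample size (15, raised to 24) belongs to the balance outcome.

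**Inputs from the article.** 24 participants at 4 sites, about 6 per session, sessions of about 60 minutes, 40% not completing.

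**Assumptions.** The 40% are absent from the T3 sessions, session and turn length do not change, and nobody's confidence changes. Where a total is needed, 480 turns per time point are assumed (60 turns x 2 sessions x 4 sites); the article gives no turn rate. All confidence levels below are assumed.

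**Step 1: count per player.**
- Remaining: 24 x 0.6 = 14.4 people, or 6 x 0.6 = 3.6 per site.
- Turns per player: 480/24 = 20 at T1 and 480/14.4 = 33.3 at T3. The ratio is 1/0.6 = 1.67 and does not depend on the assumed 480.
- With everyone confident on 40% of turns throughout, confident turns per player go from 8.0 to 13.3. The reason for leaving does not matter.

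**Step 2: percentage over all turns.** With equal turns at T1, the T1 figure is 0.4 x leavers + 0.6 x stayers, and the T3 figure is the stayers' value.

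| Leavers | Stayers | Percentage, T1 to T3 | Total confident turns, T1 to T3 |
|---|---|---|---|
| 40% | 40% | 40% to 40% | 192 to 192 |
| 30% | 50% | 42% to 50% | 202 to 240 |
| 20% | 60% | 44% to 60% | 211 to 288 |
| 50% | 30% | 38% to 30% | 182 to 144 |

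The third row, for example, is 0.4 x 0.20 + 0.6 x 0.60 = 0.44. With session time fixed, the group total follows the percentage and does not rise by 1.67. If each person instead kept the same number of turns, the total in the first row would fall from 192 to 115.

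**Step 3: simulation.** It used 24 people with fixed individual confidence averaging 40%, 14 of whom remain at T3, and 3,000 repetitions. The correlation between confidence and staying was varied.

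| Correlation | Mean change in percentage over all turns (points) |
|---|---|
| -0.5 | -7.3 |
| 0 | 0.0 |
| 0.3 | +4.2 |
| 0.5 | +7.2 |
| 0.7 | +10.0 |

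In the same runs, each remaining person's own percentage at T1 was also compared with their own at T3. The mean change lay between -0.09 and +0.04 points in every scenario, so the artefact disappears.

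**Step 4: upper limit.** Starting from 20% at T1 with equal turns, the most that loss of 40% can produce is 0.20/0.60 = 33%, reached if leavers were never confident.

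**The case against.** The strongest reply is that pooling over participants is never stated. The 20% to 80% figure is introduced as an example and would fit one person's turns as well as a group's. The sentence on time points combines sessions, not people. Each participant's turns are coded, and the design is within-participants. This stands: pooling is an inference, and the percentage part of the point is conditional on it. It does not rescue the count, because a count per participant is exactly the summary that the shrinking group inflates.

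A second reply is that all analyses are declared intent-to-treat and that missed sessions are to be accounted for. The sentence on missed sessions sits above both analysis subsections and may be meant to cover the videos, but it names no method. The abstract ties the intent-to-treat analysis and covariates to the two tests, and multiple imputation appears only under Analysis of Test and Questionnaire Data.

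A third is that a condensed article may leave the participant-level summary and model to a fuller document. That is fair, and their absence is not the complaint. The complaint is the count measure that the article does name.

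Some stronger inferences are not supported:

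- *Counts and percentages must both rise.* The percentage rises only if leavers were less confident. Illness and moves to long-term care make that plausible, but the article gives no data on it, and absenteeism need not track confidence.
- *The 67% applies to a group total.* It applies only to counts per remaining player.
- *Precision is overstated.* The video section states no test or interval to which this could attach, and Hypothesis 2, unlike Hypotheses 1 and 3, does not claim statistical significance.
- *Attrition could explain a rise from 20% to 80%.* The limit in Step 4 is 33%.

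**Conclusion.** The point holds in a limited form. A raw number of confident turns is a poor measure for Hypothesis 2: at the attrition the article itself expects, it can rise about 1.67-fold per remaining player with no change in confidence. This rests on session and turn length staying the same and on the 40% being absent from the T3 sessions; smaller losses give a smaller factor.

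A percentage over all turns, if that is what is meant, is open to bias in either direction. The size depends on an unknown difference between leavers and stayers: 16 points upward in the 20/60 illustration, nothing if they are equal, and 8 points downward in the 50/30 case.

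The matter is worth correcting but does not touch the primary balance outcome, and the article already calls the video method pilot in nature.

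**What to change.** - Do not use raw turn counts as evidence for Hypothesis 2, and replace the example measure under Objective.
- Define the outcome as each participant's proportion of their own turns completed confidently at T1, T2 and T3.
- Compare it within the same participants, with the participant as the unit: for example the mean within-person change with a 95% CI, or a model clustered on participant. State how people without footage at T2 or T3 are handled.
- Show T1 values separately for those with and without T3 footage, so that readers can see whether loss was selective.

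The cost is a little more analysis on data already to be coded turn by turn, and a smaller T1-to-T3 comparison: about 14 of 24 people at the expected attrition. That comparison describes those who remain, which is why the T1 values of the others should be shown. As the article reports that data analysis is under way, the change should be dated and disclosed.

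### One coder per site, with the facilitator coding one of the four: time-related rating bias in movement confidence cannot be traced, and comparison with the facilitator does not show that bias is reduced

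*Protocol article*

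**What the plan says.** The article's section Analysis of Video-Recorded Data fixes how movement confidence is coded.

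- **Raters:** "Video recordings will be coded by 4 independent raters, 1 of whom is the first author". The article describes this rater as the one "who is also involved in facilitating the study intervention and conducting the pretest and posttest measures".
- **Reliability check:** "We will compare the practice work of each coder for consistency using interrater reliability analysis". The threshold follows: "Once interrater reliability between the 4 raters reaches at least 80% agreement, the 4 raters will formally code the video recordings for analysis".
- **Allocation of formal coding:** "dividing up the coding so that each rater will be responsible for coding 1 of the 4 study sites (ie, 6 sessions per rater").
- **Stated safeguard:** "This will also reduce the likelihood of researcher bias", on the ground that "the work of the other 3 raters will be compared for consistency against that of the fourth rater".

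Each site contributes six recordings (sessions 1, 2, 11, 12, 19 and 20), combined in pairs into T1, T2 and T3. Study Design describes a single group, and Inclusion in Data Analysis pools the four sites. Limitations acknowledges that bias from the facilitator's combined roles is a serious risk and recommends separate people in future studies. It mentions neither the one-rater-per-site allocation nor the facilitator's role as comparison rater.

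**The concern.** Two features of the coding plan act together.

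First, rater and site are the same factor in the formal data. If one rater becomes more generous between the first and last recordings, the result is indistinguishable from a real improvement at that site. No double-coded session is stated that would show it.

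Second, the safeguard does not do what is claimed for it. The comparison rater delivers the intervention, knows the time order of the sessions, and codes a quarter of the formal material. That three others agree with this person shows that the four apply the scheme alike. It does not show that the common standard is unbiased, and the comparison can carry the facilitator's thresholds to the other sites.

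At stake is the T1-to-T3 change in movement confidence. Without a control group, a rating bias that grows with time has the same appearance as benefit.

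**Working it through.** **Inputs.** From Analysis of Video-Recorded Data: 4 raters, 4 sites, 6 recordings per site, at least 80% agreement, and example rates of 20% confident turns in week 1 and 80% in week 10. The over-scoring sizes in step 4 are assumptions.

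**1. The plan's own figure.** 4 sites × 6 recordings = 24 sessions, and 24 / 4 raters = 6 per rater. This reproduces the stated load.

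**2. What cancels and what does not.** Write the recorded score of a participant at time *t*, coded by rater *r*, as

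recorded(t) = true(t) + a_r + b_r(t),

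where a_r is constant leniency and b_r(t) is drift or expectation. Then

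recorded(T3) − recorded(T1) = true change + [b_r(T3) − b_r(T1)].

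The constant a_r drops out because the participant keeps the same rater. The bracket remains. Leniency that is not additive on the percentage scale cancels only in part.

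**3. Can the bracket be assigned to the rater?** A model with intercept, site and rater has 1 + 3 + 3 = 7 columns. Under the stated allocation its rank is 4, the same as intercept and site alone (1 + 3 = 4), so none of the 3 rater contrasts can be estimated. The same matrix applies with each participant's change as the response, so rater-specific drift and site-specific change are also inseparable. Spreading the same 24 sessions so that raters are crossed with sites gives rank 7 of 7. Crossing does not remove a bias that all raters share; that needs masking of time order and a standard independent of the facilitator.

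**4. Size if one rater or all raters over-score T3 (assumed; equal turns per site).** Pooled shift = b / 4 if one rater does so, and b if all four do.

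| Over-score at T3, b | One rater only | All four raters |
|---|---|---|
| 5 points | 1.25 | 5 |
| 10 points | 2.5 | 10 |
| 20 points | 5 | 20 |

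The article's example change is 80 − 20 = 60 points, but that is an example and not a planning value.

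**5. What 80% agreement means.** For a binary code with the same prevalence p for both raters, chance agreement is p² + (1 − p)² and kappa = (0.80 − chance) / (1 − chance).

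- p = 0.2 or 0.8: chance = 0.04 + 0.64 = 0.68; kappa = 0.12 / 0.32 = 0.375.
- p = 0.5: chance = 0.25 + 0.25 = 0.50; kappa = 0.30 / 0.50 = 0.60.

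The prevalence in the practice material is not given, so the threshold could correspond to anything in this range. It is also a minimum, and actual agreement may be higher.

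**The case against.** The case on the other side is substantial, and much of it stands.

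- **Hypothesis 2 is about change within participants, pooled over sites, and no site comparison of video data is planned.** This stands. A reader might infer that a lenient rater distorts the T1-to-T3 change. A constant additive leniency does not, because each participant stays with one rater.
- **Expectation bias comes from knowing the week, not from the allocation.** This stands in part. The allocation prevents attribution; it does not create the bias. The article does not say whether the other three raters are masked, and the full protocol may. That silence is not counted against the plan. The facilitator's knowledge of the time order follows from the stated role.
- **The threshold is agreement between all four raters.** This stands. A reader might infer that the others are trained until they match the facilitator. The text does not say so, and raters also work from operational definitions. Transfer of the facilitator's thresholds is possible, not shown. The bias-reduction sentence nevertheless rests on the comparison with the facilitator.
- **Kappa 0.375 is the unfavourable case.** This stands. If practice videos mixed the example start and end rates equally, prevalence would be 50% and kappa 0.60.
- **Random miscoding would shrink the observed change rather than inflate it.** This is true. Such attenuation is a separate matter from one rater per site and is no part of this point.
- **A site out of line would be visible.** It would, but it could not be attributed to its rater.
- **The risk is disclosed and the video method is described as a pilot.** Disclosure does not cure it. Limitations leaves separation of roles to future studies, although three other raters are already available.

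**Conclusion.** The point holds for drift and time-related expectation, and for the claim that comparison with the facilitator reduces researcher bias. It does not hold for constant leniency.

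The confounding of rater with site is complete under the stated allocation (rank 4 of 7), assuming no formal session is coded twice, since none is stated. The size of any bias is unknown. With an assumed 10-point over-score at T3 and equal turns per site, the pooled change moves by 2.5 points if one rater is affected and by 10 if all are. The agreement threshold corresponds to a kappa between 0.375 and 0.60 over prevalences of 20% to 80%, for a binary code with equal marginals, and it is applied before formal coding.

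A reader might infer that Hypothesis 2 cannot be evaluated or that the trial's main result is in doubt. Neither follows. Only movement confidence is affected; the Mini-BESTest primary outcome and its sample size do not depend on this coding. This is a worthwhile and cheap improvement, not a fatal flaw.

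**What to change.** 1. **Take the facilitator out of formal coding.** Give that share to the other three raters: 24 / 3 = 8 session-equivalents each. Keep each participant with one rater from T1 to T3, so that constant leniency still cancels.
2. **Where practical, split participants across raters within site.** With about six participants per site, that is 6 / 3 = 2 per rater at each site. Turns are taken one at a time, so they can be separated on the recordings. A lighter version splits only the facilitator's site; it links the raters, but through only two participants each.
3. **Code in random order under neutral file names.** This masks the week imperfectly, because prompts and physical support are visible on video, but it breaks the link between drift and time.
4. **Assess agreement among these three raters**, reporting kappa alongside percent agreement.
5. **Withdraw or reword the bias-reduction sentence.** It can say that the comparison checks consistency.

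The Results section says that analysis is underway. If coding is already finished, have a rater other than the facilitator recode the facilitator's site, and report the agreement.

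**Cost.** The three raters each take on one third more coding (8 / 6 = 1.33), with no extra staff. If participants are split at every site, each rater opens 24 files rather than 6 and must find the relevant turns in them, so the search time is real. Recoding after the fact is six recordings of about 60 minutes.
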